**Methods/design:**

In this study, 668 spontaneously-breathing preterm infants, born at 25^+0^ to 29^+6^ weeks’ gestation, in nasal continuous positive airway pressure (nCPAP) will be randomized to receive SRT only when the FiO2 cut-off exceeds 0.3 (control group) or if the LUS score is higher than 8 or the FiO2 requirements exceed 0.3 (study group) (334 infants per arm). The primary outcome will be the difference in proportion of infants with BPD or death in the study group managed compared to the control group.

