### Sample size

The percentage from international databases of infants with GA between 25^+0^ and 29^+6^ weeks expected to die or to develop BPD derived is approximately 40% using the Jobe and Bancalari (2001) definition [9, 10].

In a retrospective analysis of our data, the percentage of composite outcome of BPD and death at participating centers was 35%.

Assuming the percentage of newborns with death or BPD is 35% (the most conservative condition) in the control group and a decrease to 25% in the experimental group, a sample size of 668 children (334 per arm) is required to obtain a statistical power of 80% with alpha 0.05.

An interim analysis will be planned after 167 infants per arm are enrolled (334 total infants enrolled). Based on the results of the interim analysis, the study will continue to be carried out as follows:1: If the statistical *Z* test gives a value equal to or less than 0.01, the study will be terminated for futility;2: If the statistical *Z* test gives a value equal to or greater than 2.75, the study will be terminated for efficacy;3: If the statistical *Z* test gives a value less than 0.41 or higher than 0.8, the study will be continued until the previously calculated sample size is equal to 668.4: If the statistical *Z* test gives a value equal to or higher than 0.41 and equal to or less than 0.8, the final sample size will be modified, but without exceeding the maximum threshold of 1.5 times the expected initial size (sample size max: 1002).

Sample size calculations and trial simulations have been performed with R.

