### Randomization

Newborns will be allocated to one of the treatment groups (LUSG or CG) in a 1:1 ratio via a central electronically generated procedure by the e-clintrials platform (https://www.eclintrials.org/ect/) managed by [name]. The researchers will login to the platform using their personal username and password. Then a randomization form will be completed in order to verify the presence of the inclusion criteria and the absence of the exclusion criteria. Once the patient’s eligibility is confirmed, the portal will carry out an automatic randomization. Randomization is stratified by center and gestational age.

A block randomization method will be used to guarantee an adequate sample number even for the lowest GAs (25^+0^ to 26^+6^ weeks or 27^+0^ to 29^+6^ weeks).

A monthly accrual report about the study will be sent to the participating centers.

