### Primary outcome measure

Primary endpoint will be reduction of the proportion of infants with BPD (Jobe and Bancalari (2001) definition) [10] or death in the LUSG versus CG.

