### Statistical analysis

Clinical characteristics of infants in the CG and LUSG will be described using mean values and standard deviation, median and interquartile range, or rate and percentage. Univariate statistical analysis will be performed using the Student’s *t* test for parametric continuous variables, the Wilcoxon rank-sum test for non-parametric continuous variables, and Fisher’s exact test for categorical variables. A *p* value < 0.05 will be considered statistically significant.

Subsequently, clinical characteristics which are most likely associated with BPD or death will be included in a multiple logistic regression analysis to assess their independent role in predicting clinical outcome. Effect estimates will be expressed as odds ratios (ORs) with maximum likelihood-based 95% confidence limits.

The primary statistical analyses will be performed according to the intention-to-treat principle. The per-protocol analyses will be also performed with an explanatory intent. Major protocol deviations will be reported. Patients without any information available about the primary study endpoint will be classified as failure. Single imputation will be used in case of missing values will be observed for the covariates included in the adjusted and subgroup analyses.

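### The primary comparison is a difference in proportions, but the only effect estimate given an interval is an odds ratio from a logistic model with unlisted covariates

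*Protocol article*

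**What the plan says.** Three places in the protocol article put the primary comparison on the scale of proportions:

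- Abstract, Methods/design: "The primary outcome will be the difference in proportion of infants with BPD or death".
- Primary outcome measure: "Primary endpoint will be reduction of the proportion of infants with BPD" or death, LUSG against CG.
- Sample size: a control risk of 35% and "a decrease to 25% in the experimental group", from which "a sample size of 668 children (334 per arm) is required to obtain a statistical power of 80% with alpha 0.05".

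The Statistical analysis section assigns Fisher's exact test to categorical variables, with significance at p < 0.05. It then describes a multiple logistic regression on clinical characteristics thought most likely to be associated with BPD or death, to assess their independent predictive role. The effect measure follows: "Effect estimates will be expressed as odds ratios (ORs) with maximum likelihood-based 95% confidence limits". No covariates are listed and treatment arm is not named as a term. A later sentence on imputation refers to covariates in adjusted and subgroup analyses, and this regression is the only adjusted analysis described.

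The Randomization section states 1:1 allocation stratified by centre and by gestational age (25+0 to 26+6 or 27+0 to 29+6 weeks). The Statistical analysis section does not carry these strata into the comparison of arms.

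**The concern.** The outcome, the hypothesis and the sample size are all expressed as an absolute change in a proportion. The one estimate that is given confidence limits is on the odds scale. Fisher's test is specified only through its p value threshold, which gives neither an effect size nor an interval.

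Two consequences follow:

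- With about a third of control infants expected to have the outcome, an odds ratio lies well away from the risk ratio and is easily read as a larger reduction than occurred.
- An odds ratio is non-collapsible. If arm is in the model, its adjusted odds ratio depends on which covariates are included, even when the absolute effect does not change.

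What is at stake is whether the headline estimate and its interval can be set directly against the 10-point target. Randomisation was also balanced on two factors that the stated comparison of arms ignores.

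**Working it through.** **Inputs.** Control risk 0.35, experimental risk 0.25, alpha 0.05, power 80%, 334 per arm (Sample size); 1:1 allocation (Randomization). Sidedness is not stated; two-sided is assumed because it comes close to the stated size, whereas one-sided gives 259 per arm.

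**1. The stated sample size, on the scale of proportions.**
n per arm = [1.96·√(2·0.30·0.70) + 0.8416·√(0.35·0.65 + 0.25·0.75)]² / 0.10²
= (1.2702 + 0.5422)² / 0.01 = 328.5, so 329.
The plan has 334, which is within 2% of this. The size is therefore consistent with a comparison of two proportions.

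**2. Power at 334 per arm, by test.**

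| Test | Power |
|---|---|
| Two-proportion Z test | 80.7% |
| Wald test of the log odds ratio | 80.2% |
| Two-sided Fisher's exact test (enumerated) | 78.4% |

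The choice of scale hardly affects power.

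**3. The same planned result on each scale.**
- Risk difference: 0.25 − 0.35 = −0.10. SE = √[(0.2275 + 0.1875)/334] = 0.0352; half-width 1.96 × 0.0352 = 0.069. The 95% CI is about −16.9 to −3.1 points.
- Risk ratio: 0.25/0.35 = 0.714, a 29% relative reduction in risk.
- Crude odds ratio: (0.25/0.75)/(0.35/0.65) = 0.619, a 38% reduction in odds. SE of its log = √[(1/0.2275 + 1/0.1875)/334] = 0.171; 95% CI about 0.44 to 0.86.

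**4. What a fixed odds ratio says about the 10-point target.** Holding the odds ratio at 0.619:

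| Control risk | Risk difference (points) |
|---|---|
| 25% | −7.9 |
| 30% | −9.0 |
| 35% | −10.0 |
| 40% | −10.8 |
| 45% | −11.4 |

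The Sample size section itself cites both 35% (participating centres) and about 40% (international databases).

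**5. Dependence on covariates, if arm is in the model.** Keep the overall risks at 35% and 25%, and let the covariates form a normal score with SD s on the logit scale. Solve for intercepts a₀ and a₁ so that the averaged risks are 0.35 and 0.25; the conditional odds ratio is exp(a₁ − a₀).

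| Assumed s | Conditional odds ratio |
|---|---|
| 0 | 0.62 |
| 0.5 | 0.60 |
| 1.0 | 0.57 |
| 1.5 | 0.52 |
| 2.0 | 0.46 |

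The document gives no value for s, so this table is an illustrative range. The absolute difference is 10 points in every row.

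**The case against.** The strongest reply has four parts.

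- **The powered hypothesis is tested.** Fisher's test at the end and the Z test at the interim both address equality of two proportions. This stands. A reader might infer that the trial would not estimate or test what it is powered on. The document does not support that: step 2 shows nearly the same power on each scale, and a crude difference with an interval can be computed from the two arm percentages and denominators.
- **The logistic model may be purely prognostic.** It is introduced as a follow-on analysis, its stated aim concerns the clinical characteristics, and arm is not named. This also stands, so it cannot be said that the odds ratio is definitely the treatment-effect estimate. It does not remove the point. If arm is in the model, the treatment effect is a conditional odds ratio; if it is not, the odds-ratio sentence gives no treatment effect at all. On neither reading does the stated analysis attach an interval to the primary difference.
- **An article condenses, and the analysis plan may name the estimator.** That is fair for interval methods and covariate lists, and their absence is not the finding. The article does, however, positively state the effect measure. If an analysis plan names a risk difference as the primary estimate, this sentence needs to be aligned with it.
- **Odds ratios are a valid summary.** They are, and nothing here makes them wrong as secondary results. They are simply not the quantity that the article calls primary.

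**Conclusion.** The point holds as a misalignment of the effect estimate, not as a fault in the test or the sample size. The primary quantity is a difference in proportions, the only estimate with a stated interval is an odds ratio from an unspecified model, and the final comparison of arms does not use the randomisation strata.

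At the planned rates, the same result reads as 10 points, a 29% relative reduction in risk or a 38% reduction in odds. These figures rest only on the article's 35% and 25%. The spread of conditional odds ratios from 0.60 to 0.46 rests on assumed covariate strengths and on arm being in the model; it shows the direction of the problem, not its size in this trial. The correction is worthwhile, but the trial's conclusion on its hypothesis does not depend on it.

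**What to change.** In the Statistical analysis section, state that the primary effect estimate is the LUSG minus CG difference in the proportion with BPD or death, with a 95% CI, adjusted for the randomisation strata. Two routes are suitable:

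- a Mantel-Haenszel risk difference over centre by gestational-age stratum; or
- standardisation from a logistic model containing arm, gestational-age stratum and centre.

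With 18 active centres and two gestational-age bands there are 36 cells, so 668 infants average about 19 per cell (668/36 = 18.6). The variance estimator should therefore be one suited to sparse strata. Report the risk ratio alongside, keep adjusted odds ratios as secondary, and say whether arm is a term in that model.

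The cost is a few sentences and a few lines of code. No new data are needed and the sample size is unchanged. Trial status reports 213 infants enrolled on 25 September 2023, against an interim analysis at 334, so at that date the change could still precede any planned comparative look.

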### Additional analyses

An interim analysis will be planned after 167 infants are enrolled for each arm (334 total infants enrolled). The analysis will aim to compare treatment arms with respect to efficacy, safety, futility, and, if necessary, a sample size adjustment. In the interim, the prespecified stopping rules for safety are: a mortality rate > 40%, a rate of severe IVH > 30%, and a pneumothorax rate of > 10% in the LUSG compared to CG. The interim analysis will be performed by an independent statistician, blinded for treatment allocation. The statistician will report to the independent Data and Safety Monitoring Board (DSMB) which will have unblinded access to all data and will discuss the results of the interim analysis with the Steering Committee in a joint meeting. The Steering Committee will decide whether to continue the trial and will report to the central Ethics Committee.

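### The mortality stop (> 40%) lies above the whole death-or-BPD rate expected in either arm, and the scale of the safety limits is not stated

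*Protocol article*

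**What the plan says.** The Additional analyses section of the protocol article plans one interim analysis at 167 infants per arm (334 in all). It lists the prespecified safety stops as "a mortality rate > 40%, a rate of severe IVH > 30%, and a pneumothorax rate of > 10" per cent, followed by the qualifier "in the LUSG compared to CG". It gives no scale for the limits and no expected rate for any of the three events.

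The Sample size section supplies the only event rates in the document, all for the composite of death or BPD:

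- International databases: infants "expected to die or to develop BPD derived is approximately 40" per cent.
- The trial's own centres: "the percentage of composite outcome of BPD and death at participating centers was 35" per cent.
- Design, control arm: "Assuming the percentage of newborns with death or BPD is 35% (the most conservative condition) in the control group".
- Design, LUSG: "a decrease to 25% in the experimental group".

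The Primary outcome measure section confirms that death is one component of that composite.

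**The concern.** Deaths are a subset of death-or-BPD events, so mortality in an arm cannot exceed that arm's composite rate. A mortality limit above 40% is higher than the 35% expected for the composite in controls and the 25% expected in the LUSG. It is no lower than the international figure of about 40%. Read as an absolute rate, the limit could be reached only if the trial's planning figures were badly wrong, or after a catastrophe that no board would need a rule to see.

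The qualifier about comparison with the control group leaves three readings open: an absolute rate in the LUSG, a percentage-point excess over controls, or a relative increase over controls. They behave very differently. Two make the mortality stop inert, and the third makes it fire often by chance.

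At stake is the one prespecified trigger that looks at deaths separately from BPD, in an open trial of infants born at 25+0 to 29+6 weeks.

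**Working it through.** **Inputs from the document.** Composite 35% (CG) and 25% (LUSG), about 40% in international databases; 334 per arm, 80% power, alpha 0.05 (Sample size); 1:1 allocation (Randomization); 167 per arm at the interim and limits of 40%, 30% and 10% (Additional analyses).

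**Assumed, because the document gives no figures.** Control mortality 5% to 20%, severe IVH 5% to 15%, pneumothorax 3% to 10%. The only bound in the document is that mortality cannot exceed the composite.

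**1. Reproducing the plan's own figure.** Two proportions, two-sided, pooled variance:

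n = [1.96·√(2·0.30·0.70) + 0.8416·√(0.35·0.65 + 0.25·0.75)]² / 0.10² = (1.270 + 0.542)² / 0.01 ≈ 329 per arm, or 658 in all.

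The plan states 668, and power at 334 per arm is 80.7%. The composite rates are therefore the ones the design really uses.

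**2. Absolute rate in the LUSG.** 0.40 × 167 = 66.8, so the limit needs at least 67 deaths. The design expects 0.25 × 167 ≈ 42 to 0.35 × 167 ≈ 58 composite events per arm. P(fire) = P(X ≥ 67), with X binomial (167, p):

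| True LUSG mortality | P(fire) |
|---|---|
| 20% | 2e-9 |
| 25% | 1e-5 |
| 30% | 0.003 |
| 35% (every control-rate composite event a death) | 0.097 |
| 40% | 0.52 |

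The 35% row uses only the document's own bound. For comparison, 20% against 10% gives Z = 0.10 / √(0.15·0.85·2/167) = 2.56 in expectation, a signal that the limit would almost never pick up.

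**3. Percentage-point difference.** A gap above 40 points needs at least 67 more deaths in the LUSG than in controls. Exact enumeration over two binomials of 167 gives P(fire) = 1.5e-6 for 30% v 10% and 0.013 for 40% v 10%. With equal true rates it is essentially zero.

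**4. Relative increase.** The limit fires when LUSG deaths exceed 1.4 times control deaths. With no true difference:

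| Mortality in both arms (assumed) | P(fire) |
|---|---|
| 5% | 0.24 |
| 10% | 0.15 |
| 15% | 0.10 |
| 20% | 0.06 |

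**5. The other two limits.**

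- Severe IVH, absolute > 30%, needs 51 of 167. P(fire) is 0.0008 at a true 20%, 0.06 at 25% and 0.90 at 35%: blunt, but not dead.
- Pneumothorax, absolute > 10%, needs 17 of 167. P(fire) is 0.004 at a true 5%, 0.80 at 12% and 0.97 at 15%.
- Pneumothorax as an excess above 10 points: P(fire) is 0.00002 at 5% v 5%, 0.001 at 10% v 10%, 0.51 at 15% v 5% and 0.93 at 20% v 5%.
- Pneumothorax as a ratio above 1.1 with no true difference: 0.39 to 0.43 at rates of 3% to 10%.

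**The case against.** **Other protections exist.** The futility rule in the Sample size section stops the trial at the same interim when Z ≤ 0.01, on a composite that includes death. Suppose mortality rises from 10% to 20%, non-fatal BPD is unchanged, and positive Z favours the LUSG. The composite is then 35% v 45%, and that rule stops the trial with probability 0.97. If the extra deaths wholly replace BPD cases (35% v 35%), the probability is about 0.52. The DSMB also has unblinded access to all data, and serious adverse events are reviewed during the trial. This stands as mitigation: the 2e-9 figure describes one limit, not the chance that the trial stops. It does not repair the limit. If BPD fell enough for the composite to reach its design values of 35% v 25%, expected Z would be 0.10 / √(0.30·0.70·2/167) ≈ 2.0. The futility rule would then stop in only about 3% of trials, whatever the split between deaths and BPD.

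**The safety rule as a whole is not useless.** A reader might infer that none of the stops can detect harm on any reading. The figures for pneumothorax contradict that.

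**Chance firing is not general.** A reader might infer that any comparison with controls would fire on noise. That holds only for a relative increase, arguably the least natural reading of the words, and it rests on assumed event rates. A point difference almost never fires by chance.

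**The word joining the limits.** One could read the text as requiring all three together. The section speaks of stopping rules in the plural and then lists them, so the conjunction most naturally closes the list. A clarifying phrase is worthwhile, but this is not a defect in itself.

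**Detail belongs in a charter.** The exact test and boundary may well sit in a DSMB charter or the full protocol, and their absence from an article is no finding. But the article prints the levels, and no definition of an absolute rate or point difference brings 40% mortality into line with a 35% composite.

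**Conclusion.** The point holds for the mortality limit. It is set above the expected death-or-BPD rate in both arms, and the document does not say on which scale the three limits work. As an absolute rate it is inert: even if every composite event at the control rate were a death, it would fire with probability of only about 0.10. As a 40-point difference it is more so. As a relative increase it would fire with no true difference in about 6% to 24% of trials.

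The comparison of 40% with 35% and 25%, and the 0.097 figure, rest on the document alone. The other probabilities depend on component rates that the document does not give, and are shown over a range. The severe IVH limit is blunt under those assumptions. The pneumothorax limit can work as an absolute rate or a point difference. The primary estimate and the type I error rate are unaffected.

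**What to change.** In the Additional analyses section, or by a dated addition to the DSMB charter that the section cites:

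1. Reconcile the mortality level with the composite rates in the Sample size section.
2. State one scale for all three limits, and that any one of them suffices for DSMB review.
3. Express the mortality stop as a between-arm comparison at a level the DSMB fixes before the 334-infant interim. For illustration only, Z ≥ 2 against the LUSG at 167 per arm detects 10% v 20% mortality with probability about 0.72, and gives a false alarm in about 2.3% of trials with no true difference. The boundary itself is for the DSMB to choose.

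The cost is a wording amendment with its ethics notification; no new data are needed. The downside is a small chance of an unneeded safety review. The Trial status section reports 213 infants enrolled on 25 September 2023, so the interim had not been reached at that date. If it has since taken place, the DSMB should record which reading it applied.

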### Definition of study conclusion

The study will be considered concluded for each patient at the time of discharge or death or in case of withdrawal of consent. The study will be considered definitively concluded upon discharge or death or withdrawal of consent of the last patient enrolled.

### Withdrawal of subjects

Parent(s) or legal guardian(s) may withdraw consent to participate in the study at any time.

### Ethical considerations

This study will be conducted in accordance with the Declaration of Helsinki, Edinburgh revision (2000), with the directive CPMP/ICH/135/95, implemented by the Ministerial Decree of 15 July 1997 (Good Clinical Practice) and in accordance with the Ministerial Decree of 10 May 2001 published in the Official Gazette no. 139 of 18 June 2001. In this regard, the medical interventions and laboratory and instrumental analysis procedures envisaged by this protocol are normally considered to be of good clinical practice in patients of this type.

The protocol has been approved by the Tuscan Pediatric Ethical Committee protocol n. 302/2021, with amendment n. 278–2/2022.

### Quality control and quality assurance procedures

Compliance will be defined as full adherence to protocol. Compliance with the protocol will be ensured by several procedures as described below.

### Site set-up

Local principal investigators are required to participate in preparatory meetings in which details of study protocol, data collection, and procedures in control and lung ultrasound group will be accurately discussed. All centers will receive detailed written instructions on web-based data recording and, to resolve possible difficulties, the Clinical Trials Coordinating Center (Careggi University Hospital of Florence, Florence, Italy) will be available for assistance.

### Enrollment procedure

Obstetricians from the different hospitals will be aware of the study protocol and will inform the neonatologist of high-risk preterm births.

The study information leaflet will be provided and explained to parents, relatives, and guardians of eligible patients in the hours preceding birth by trained staff. Parents’ consent must be obtained within 180 min following birth and before the randomization procedure. In cases of spontaneous preterm labor and subsequent vaginal or cesarean delivery, the informed consent will be obtained immediately after birth.

Risks and benefits will be fully discussed. Parents will be informed that the study does not include blood sample or other interventions other than those routinely performed in the NICU.

Informed consent will be obtained by the principal investigator of each center or the collaborators in charge. The patients will be enrolled by the principal investigator or the collaborators in charge at the time of the delivery.

